**SAP Version History**

| Protocol version | SAP version no | Version Date | Changes/Revisions |
|------------------|----------------|--------------|-------------------|
| 1.4              | 1.0            | 24.03.2021   | First version     |
|                  |                |              |                   |
|                  |                |              |                   |
|                  |                |              |                   |

## **1. Introduction**

### **1.1 Purpose and Scope of the Statistical Analysis Plan**

This statistical analysis plan (SAP) details the proposed statistical analysis of the primary and secondary variables and other data resulting from the European & Developing Countries Clinical Trials Partnership (EDCTP) funded randomized, blinded non-inferiority trial on the immunogenicity and safety of fractional doses of yellow fever vaccines (NIFTY) in Kenyan and Ugandan adults and children. The results reported in the main paper(s) reporting results from this trial should follow the strategy set out in this document. Subsequent analyses of a more exploratory nature will not be bound by this strategy, though they are expected to follow the broad principles laid down here. The principles are not intended to curtail exploratory analysis, nor to prohibit accepted practices (such as data transformation prior to analysis), but they are rather intended to establish the rules that will be followed, as closely as possible, when analysing and reporting the trial.

The analysis strategy will be available on request when the principal papers are submitted for publication in a journal. Suggestions for analyses by journal editors or referees will be considered carefully and carried out, as far as possible, in line with the principles of this analysis plan; if reported, the source of the suggestion will be acknowledged.

Any deviation(s) from the SAP will be described and justified in the final report of the trial. The analysis should be carried out by an identified, appropriately qualified and experienced statistician, who should also ensure the integrity of the data during their processing through quality control and evaluation procedures.

### **1.2 Trial Summary**

In July 2016, the demand for yellow fever (YF) vaccines in response to the large urban outbreaks occurring concurrently and the risk of further spread through Africa and to Asia was larger than the available global supply. In this situation, the World Health Organization (WHO) developed recommendations for the use of fractional doses of YF vaccine as a dose-sparing strategy. These recommendations were based on data from a limited number of clinical trials, none of which had been conducted in Africa. Additional studies were initiated to assess the applicability of fractional doses to all four WHO-prequalified YF vaccines with respect to vaccine immunogenicity in adults and children in Africa, including HIV positive adults. One such study, comparing full standard dose to 1/5th of standard dose of all four WHO-prequalified YF vaccines in adults (Clinicaltrials.gov number: NCT02991495), is currently ongoing at KEMRI CGMRC (see SERU protocol 3452) and Epicentre, Mbarara (UNCST HS 2237) and is designed to answer questions on the use of current stock of YF vaccines with a potency as close as possible to each manufacturers' minimum release. Data from this trial will inform a WHO recommendation on using 1/5th of the current standard dose of vaccine for outbreak control. However, since many vials will contain excess YF vaccine such that 1/5th of a vial is

likely to be substantially above the current minimum potency requirements, these data may not be scientifically explanatory regarding the minimum dose required for preventive use. Here, in this new complementary study, we aim to determine the lowest YF vaccine dose that is non-inferior to the current standard full dose among populations in sub-Saharan Africa (SSA). The study will be conducted in Kenya (KEMRI CGMRC, Kilifi) and Uganda (Epicentre, Mbarara) with trial participants recruited at both sites, using vaccine from one WHO-prequalified manufacturer (Institut Pasteur de Dakar, Senegal). Our primary aim is to compare the immunogenicity of full standard dose of vaccine with three lower doses in adults, using seroconversion at 28 days post-vaccination, measured by plaque reduction neutralization assay (PRNT50), as the endpoint. Adult participants (n=480) will be randomized for vaccination with full standard dose or with approximately 1000, 500 or 250 IU of vaccine (i.e. 4 arms, 1:1:1:1 allocation ratio). Safety and immunogenicity results will then be reviewed by the study Data and Safety Monitoring Board (DSMB), and the lowest non-inferior dose selected for assessment in a sub-study in children (n=420) in comparison to full standard dose (i.e. 2 arms, 1:1 allocation ratio) co-administered with the Expanded Program for Immunisation (EPI) Measles vaccine. Secondary objectives will include immunogenicity at 10 days, 1 year and 2 years post-vaccination, assessment of the influence of cross-reactive antibodies to other flaviviruses on vaccine immunogenicity, assessment of T and B cell immune responses, assessment of virologic and immunological kinetics and occurrence of serious adverse events (SAE). In addition, we will assess the range of views and perceptions of key stakeholders in vaccine policy and implementation on lower vaccine dose usage during YF epidemics and routine use. We expect the data from this qualitative study to inform the implementation of policies relating to low-dose vaccine usage for the control of YF and other diseases (e.g. pneumococcal vaccines) where such strategies are in consideration.

## **2. Study Objectives**

### **2.1 Primary Objectives**

To determine the lowest dose (1000, 500 and 250 IU/dose) of YF vaccine that is non-inferior to the full standard dose as measured by seroconversion using the PRNT50 assay at 28 days post-vaccination.

Seroconversion is defined as a  $\geq 4$ -fold rise in neutralizing antibody titre between pre-immunization (Day 0) and post-immunization samples. Any patient who appears seronegative (PRNT50 value below the Limit of Quantification, 1:10) will be considered to have a baseline titre of LOQ/2, 1:5.

Noninferiority will be assessed by comparing the lower dose to the full dose of vaccine. Since baseline antibody levels can modulate response to the vaccine, the primary analysis will be based on the per-protocol (PP) population, which must be seronegative to YF at baseline. Secondary analysis of seroconversion at Day 28 will be performed in the intent-to-treat (ITT) population, regardless of baseline YF seropositive, and for the subset of adults which are seropositive to YF at baseline. The primary analysis time point will be when each participant has provided a Day 28 post-vaccination blood sample or has surpassed the window (+/- 3 days) to provide this sample.

### **2.2 Secondary Objectives**

There are multiple secondary objectives to assess non-inferiority, safety, and immunogenicity in specific populations. These are:

- To describe the geometric mean PRNT50 titre (GMT) at 10 days, 28 days, 1 year and at 2 years post-vaccination of the different doses of the YF vaccine.
- To describe the change in PRNT50 titre (i.e. the geometric mean fold increase (GMFI) as a continuous variable) between baseline and day 28 after vaccination with the different doses of the YF vaccine.
- To measure neutralizing antibody to other flaviviruses (including dengue, West Nile and Zika viruses) on the baseline sample and determine the impact of these antibodies on YF vaccine immunogenicity.
- To assess post-vaccination control of viremia by vaccine dose on samples collected at baseline, and on days 2, 3, 4, 5, 6, 7 and 10 after vaccination.
- To determine the change in T and B cell immune responses between baseline and days 10 and 28 post-vaccination.
- To determine the change in serum cytokine and chemokine levels between baseline and days 2, 3, 4, 5, 6, 7, 10 and 28 post-vaccination.
- To assess the occurrence of adverse events (AE) over 28 days after vaccination and serious adverse events throughout the duration of the study.
- Map out key stakeholders' priorities and perceptions regarding a change in policy towards the use of lower doses of YF vaccine and their potential influence on policy process.

Once results for the main outcome are obtained, data will be reviewed by the study DSMB. The DSMB will then decide if the study should proceed to the second phase where the lowest non-inferior dose, as measured at day 28 in the adult study, will be selected for assessment in children aged 9-12 months co-administered with the Measles vaccine. The aim of these studies will be to: assess the non-inferiority in seroconversion of the lower dose compared to the full standard dose as measured by PRNT50 at 28 days post-vaccination.

### **3. Study Design and Assessment**

#### **3.1 Study Design**

##### **3.1.1 Study Cohorts**

We will use YF vaccine produced by the Institut Pasteur de Dakar, Senegal. One vial format will be provided. It will contain standard full dose of vaccine for administration in 0.5ml per dose. A second vial will be prepared from a standard vial to contain vaccine diluted to approximately 1000 IU/dose for administration in 0.5ml per dose. Fractional volumes of this second vial will be administered as per manufacturer's instructions to achieve the 500 IU and 250 IU doses. There will be two study cohorts of interest:

A: General adult population (n=480); and

B: Children 9-12 months (n=420)

Results for the safety and primary outcome of the adult study will then be reviewed by the DSMB, and the lowest non-inferior dose in the adult study selected for assessment in children aged 9 -12

months sub-study. Should there be evidence of inferiority of the lower dose vaccine, the sub-studies in populations (B) will not be conducted.

### 3.1.2 Inclusion Criteria

The inclusion criteria will be used at screening to identify participants eligible for the study and will be checked prior to vaccination to confirm ongoing eligibility.

- For cohort (A) Individuals aged  $\geq 18$  -  $< 60$  years of age.
- For cohort (B) (i.e. children): Individuals 9-12 months
- HIV negative on serological screening OR
- HIV positive adults on serological testing, and no symptoms suggestive of current clinical immunosuppression and CD 4 count  $> 200$  (for adults) and CD4%  $> 25\%$  (for children) within the last 6 months.
- Ability to provide informed consent to participate in the study

### 3.1.3 Exclusion Criteria

- Known contraindications to YF vaccination such as allergies to egg protein and chicken products or any component of the vaccine (including gelatin, eggs, eggs products or chicken products), immunodeficiency, known thymus disorder, such as thymoma and myasthenia gravis
- Using corticosteroids or other immunosuppressive therapy
- Thymus disorder, such as thymoma and myasthenia gravis
- Acute febrile disease on the day of vaccination with temperature  $> 37.5$  degrees Celsius is a temporal contraindication.
- Previous YF vaccination
- Previous YF infection as determined from history
- Pregnancy (as determined by a urine test on the proposed day of vaccination) and lactating women
- Planning to migrate out of the study areas before the end of the study follow-up
- Planning to travel to a country requiring YF vaccination certificate within the first year after vaccination.
- Any condition or criteria, including acute or chronic clinically significant abnormality that in the opinion of the investigator might compromise the wellbeing of the volunteer or interfere with the outcome of the study.

### 3.1.4 Withdrawal/Discontinuation Criteria

In accordance with the principles of the Declaration of Helsinki, participants have the right to withdraw from the study at any time and for any reason and are not obliged to give their reason for doing so.

Participants may be discontinued for the following reasons:

- SAE which requires discontinuation of study involvement or which results in inability to continue to comply with study procedures;
- Protocol violation requiring discontinuation from study;

- Withdrawal of consent;
- Participant moves out of the study area and/or cannot be traced
- Any other reason determined by participant or study staff

The study team will continue to follow up all participants, with their agreement, until the end of the study. The reason for withdrawal will be recorded in the Case Report Form (CRF). If withdrawal is due to a SAE, appropriate follow-up visits or medical care will be arranged, with the agreement of the participant, until the event has resolved. Following Good Clinical Practice (GCP) guidelines, data on participants who specifically withdraw their consent for use of their data will not be included in the data analysis. However, participants who withdraw from follow up without withdrawing consent for use of their data will be included.

### **3.2 Sample Size and Power Considerations**

This study will be powered to detect non-inferiority of each lower dose of vaccine (1000 IU, 500 IU, 250 IU) compared to the full standard vaccine dose.

For the adult study, assuming a 95% seroconversion rate, 90% power, 2.5% level of significance for a one-sided test and a non-inferiority margin of 10%, which gave a sample size of 100 per arm. The 10% non-inferiority margin was chosen in consideration of the public health consequence of a loss of protection but a potential increase in vaccine dosages in a situation where vaccine stocks are insufficient to respond to an outbreak. The sample size was increased by 20% to account for: i) losses to follow up and, ii) unevaluable participants with a positive serological response for YF virus at baseline. Thus, a total sample size of 480 will be required for the four vaccine dose groups (i.e. full dose, 1000 IU, 500 IU and 250 IU).

For the study in children, we assumed a 90% seroconversion rate (accounting for lower vaccine immunogenicity reported in children [4]), 90% power, 2.5% alpha for a one-sided test and a non-inferiority margin of 10%, which gave a sample size of 190 per arm. This was increased by 10% to account for 5% losses to follow up and 5% unevaluable participants with a positive serological response for YF virus at baseline. This gave a total sample size of 420 (i.e. 210 in the full dose group and 210 in the lower dose group).

Analyses of all other efficacy and safety endpoints are supporting only. Therefore, no significant adjustments will be made for multiple comparisons.

### 3.3 Randomization and Blinding

Consenting participants who have satisfied all the eligibility criteria and completed the baseline assessment will be randomized to receive one of the four vaccine doses. The allocation will be to one of the four treatment arms per a computer-generated randomization schedule. Randomization will be done by randomization booklets with concealed scratch cards, allocated in order of recruitment and opened on the day of vaccination. These will be prepared by a person outside the study. To minimize vaccine wastage, randomization will be done in block sizes that match with clinic visit days. Allocations will be concealed until a member of the unblinded study team scratches the randomization booklet to reveal the participants' randomization arm.

All participants will receive the same information regarding adverse events. Participants will not be informed of the allocated vaccine. The vaccine will be prepared outside of the view of the participants.

The children will be randomized to either full dose or the lowest non-inferior dose of the vaccine. The vaccine dose to be used will be selected based on the safety and immunogenicity results at day 28 post-vaccination from the adult study. Similar randomization procedures as the adult study will be used. The children will be vaccinated in collaboration with a Ministry of Health EPI clinic for the Measles vaccine.

### 3.4 Selection of lowest non-inferior dose group for sub-study

Following the primary analysis time point, the DSMB will determine whether there is sufficient evidence of efficacy and safety to continue the trial in Cohort(B) and will offer a recommendation on which lowest non-inferior dose group to use in the sub-studies.

First, the DSMB shall assess non-inferiority at Day 28 of seroconversion rates (primary analysis), GMT, and GMFI for each dose groups in the adult PP and ITT populations. Any vaccine dose group (i.e.1000 IU, 500 IU, 250 IU) that is shown to be non-inferior in seroconversion and for which no concerns regarding significant variation are noted on secondary analysis will be considered for use in the sub-studies. If the lower doses are inferior to the full dose of all four vaccines, the sub-studies in populations (B) will not be conducted.

The primary endpoint will be assessed 28 days post-vaccination, but study visits will continue for up to two years after vaccination. Venous blood samples for YF titre quantification by PRNT will be collected at baseline, Viremia visit (2-7 days), 10 days (+/- 1 day), 28 days (+/- 3 days), 1 year (+/- 14 days) and 2 Years (+/- 28 days) after vaccination. PRNT for paired samples will be run at the same time to assure comparability of measurements from samples at baseline, 10 days, 28 days, 365 days and 2 years post-vaccination. The quantification of antibodies will be done at the Institut Pasteur in Dakar, Senegal. PRNT is considered the most sensitive and specific test for quantification of neutralizing antibodies and is the reference method for assessing immune response after vaccination.

*Table 1: Study activities timeline*

| Procedure                                     | Screening
Day -30* | Day 0            | Day 2, 3,
4, 5, 6, 7** | Day 10
(+/- 1 day) | Day 28
(+/- 3 days) | Day 365
(+/-14
days) | Day 730
(+/- 28
days) |
|-----------------------------------------------|-----------------------|------------------|---------------------------|-----------------------|------------------------|----------------------------|-----------------------------|
| Informed Consent                              | X                     |                  |                           |                       |                        |                            |                             |
| HIV Antibody test                             | X                     |                  |                           |                       |                        |                            |                             |
| Pregnancy test                                | X                     | X                |                           |                       | X                      |                            |                             |
| Demography                                    | X                     | X                |                           |                       |                        |                            |                             |
| Vital signs                                   | X                     | X                |                           | X                     | X                      | X                          | X                           |
| History and Physical exam                     | X                     |                  |                           | X                     | X                      | X                          | X                           |
| Randomization                                 |                       | X                |                           |                       |                        |                            |                             |
| Vaccination                                   |                       | X                |                           |                       |                        |                            |                             |
| Blood sample
(Adults, Children)            |                       | X
(10ml, 6ml) | X
(4ml, 4ml)           | X
(10ml, 6ml)      | X
(10ml, 6ml)       | X
(10ml, 6ml)           | X
(10ml, 0ml)            |
| Cumulative blood volume
(Adults, Children) |                       | 10ml, 6ml        | 14ml, 10ml                | 24ml, 16ml            | 34ml, 22ml             | 44ml, 28ml                 | 54ml, 28ml                  |
| Adverse events and serious
Adverse Event   |                       |                  | X                         | X                     | X                      | X                          | X                           |

\*Before vaccination. Screening can occur between 0 and 30 days before vaccination. Screening and vaccination can occur on the same day, but participants that are not recruited within 30 days will be re-screened.

\*\*All participants will be randomized to provide one 4ml blood sample at one of 6 time points (days 2, 3, 4, 5, 6, or 7).

*\*Note that vaccination will generally occur on same day of enrolment, but under certain circumstances may necessarily be delayed to a later date. Day 0 will always be considered date of vaccination.*

### 3.5 Definition of Analysis Populations

The per-protocol (PP) population will include randomized participants who have a blood sample at baseline and 28 days (+/- 3 days) post-vaccination, who are seronegative (PRNT50 <1:10) to YF at baseline and for whom the eligibility criteria were correctly applied. The intention-to-treat (ITT) population will comprise all randomized participants who received a dose of a study vaccine and that have at least one post-vaccination blood sample. We will also assess immunogenicity endpoints for the subset of the ITT population which has a pre-existing YF neutralizing antibodies (PRNT50 ≥1:10) at baseline (ITT YF+). As above, the same definitions will be applied to the sub-population to generate, Children ITT and Children ITT YF+ populations. The same noninferiority and safety endpoints assessed for the PP and ITT populations will be analyzed for cohort (B).

The safety (SAF) population will include all participants who received a study vaccine.

### 3.6 Protocol Deviations

Any deviation from protocol-specified procedures and study-related SOPs occurring during the conduct of the trial will be documented and reported as protocol violations (major deviations) or minor deviations, as defined in the protocol. Protocol violations will be reported to the Sponsor and

reviewing ethical committees, as appropriate and in accordance with the requirements of the involved committees. A final Protocol Deviation Listing will be generated and reviewed blindly by sponsor personnel prior to freezing the database to ensure that all important deviations, including those that may lead to exclusion from analysis, are captured and summarized. No formal statistical testing will be undertaken.

Subjects will be excluded entirely from analysis if they have a protocol deviation defined as a full exclusion that affects the validity of all their data (e.g. failure to obtain informed consent). Subjects with a partial protocol deviation (e.g. moving away from study area) will be included up until the time of the deviation; from this point onwards, their data will be excluded from analysis. If a deviation affects data at a specific time point (e.g. blood sample not taken within defined time window), only data affected by the deviation will be removed from analysis.

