### 9.4. Withdrawal criteria

In accordance with the principles of the current revision of the Declaration of Helsinki, a participant has the right to withdraw from the study at any time and for any reason and is not obliged to give his or her reasons for doing so. In addition, the participant may be withdrawn for any of the following reasons:

- Participant non-compliance with study requirements (for example follow-up visits) despite reminders and attempts to make contact
- Participant moves out of the study area and cannot be traced
- A SAE, which requires discontinuation of the study involvement or results in inability to continue to comply with study procedures

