### 9.5. Managing withdrawals

The study team will continue to follow up all vaccine recipients, with their agreement, until the end of the study wherever possible. The reason for withdrawal will be recorded in the Case Report Form (CRF) if given. If withdrawal is due to a SAE, appropriate follow-up visits or medical care will be arranged, with the agreement of the participant, until the event has resolved, stabilized or a non-study related causality has been established. Following Good Clinical Practice (GCP) guidelines, data on participants who specifically withdraw their consent for use of their data will not be included in the data analysis. However, participants who withdraw from follow up without withdrawing consent for use of their data will be included.

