### 5.2 Methods for Handling Missing Data

The numbers (with reasons) of losses to follow-up (dropouts and withdrawals) over the course of the trial will be reported by trial arm. Valid inferences will be made under the missing at random assumption. No imputation will be done in any way.

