#### *Secondary Non-Inferiority Analysis*

Secondary analyses will include assessment of seroconversion in the ITT population as a whole, on the subset of the ITT population with baseline seropositivity to YF, and in the subset of the PP population with no reported history of flavivirus infection. Geometric mean PRNT50 titre (GMT) and GMT fold increase (GMFI) and corresponding 95% confidence intervals (CI) on day 0 and 28 will be calculated. Non-inferiority will be calculated by the difference in GMT and GMFI between the full dose and each lower dose group. Titres will be graphically represented by reverse cumulative distributions obtained by plotting, for each possible value of the titre (abscissa), the proportion of subjects with a titre greater than this value.

Lower vaccine doses may change the kinetics of antibody response. The assessment of seroconversion rates, GMT, and GMFI 10 days after vaccination in the ITT population will provide important information in the context of low dose vaccine usage in outbreak response. These three immunogenicity outcomes will also be assessed at 1 year and 2 years post-vaccination in the ITT population to confirm a lasting effect of full and low dose vaccination.

Relationships between seroconversion and vaccine immunogenicity (PRNT50 GMT and GMFI) will be related to frequencies of specific T and B cell subsets measured by flow cytometry, chemokine and cytokine levels in sera and neutralising antibody levels to other flaviviruses. Correlations between vaccine viraemia and immunogenicity will be assessed across the different vaccine dose strata. Comparisons of immune and viraemia kinetics will be made between the adult and children trial participants using non-parametric tests, whilst accounting for the administered vaccine dose.

Adverse events occurring during the study follow up period will be analyzed and compared between groups. This will be a descriptive analysis and will include all AEs up to 28 days post-vaccination, and SAEs that occurred any time during study follow-up.

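### SAP 3.6 excludes all data after a participant moves away, so valid 1- and 2-year titres from movers who still attend would be dropped from the ITT durability analyses

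*Supplement*

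**What the plan says.** SAP 3.6 (Protocol Deviations) has three tiers. A full exclusion removes a participant entirely. A fault at one time point removes only the affected data. Between them is the partial deviation, whose only example is the mover: "moving away from study area) will be included up until the time of the deviation; from this point onwards, their data will be excluded". The exclusion is from analysis in general; the population is not specified.

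Other sections treat the same person differently:

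- **Protocol 9.4** lists as a possible reason for withdrawal: "Participant moves out of the study area and cannot be traced". Both conditions must hold.
- **SAP 3.1.4** has "Participant moves out of the study area and/or cannot be traced" as a reason for which a participant may be discontinued. The same section then says: "The study team will continue to follow up all participants, with their agreement, until the end of the study".
- **Protocol 9.5**: "The study team will continue to follow up all vaccine recipients, with their agreement, until the end of the study wherever possible".
- **SAP 3.5** defines the ITT population as "all randomized participants who received a dose of a study vaccine and that have at least one post-vaccination blood sample". Residence plays no part.
- **SAP 5.3.2**, on seroconversion, GMT and GMFI: "These three immunogenicity outcomes will also be assessed at 1 year and 2 years post-vaccination in the ITT population to confirm a lasting effect".
- **SAP 5.2**: "No imputation will be done in any way".

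**The concern.** A change of address does not invalidate a neutralisation titre. The rule therefore removes usable measurements from a set labelled ITT because of a post-randomisation event unrelated to the assay, and no reason is given. It can only matter for movers who still attend, since untraceable movers have no later data to exclude. Those who do attend would give blood for a result that the analysis ignores.

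The tables at stake are those meant to show that a low dose lasts: adult Tables 2.6, 2.7, 2.19, 2.20, 2.32 and 2.33, and children's Tables 2.13, 2.26 and 2.39. Durability matters for any low-dose policy, although these analyses are secondary.

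Safety is a side issue. SAP 4.2.1, 5.3.2 and 5.3.3 count SAEs at any time over the whole safety population. They are more specific than 3.6 and should govern, so no loss of SAEs is claimed.

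**Working it through.** **Step 1: follow one participant through the text.** Take an adult vaccinated at Kilifi who moves away in month 8, stays in telephone contact and returns for the Day 365 and Day 730 visits.

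| Source | Status of this participant |
|---|---|
| Protocol 9.3 | Eligible: only migration planned at entry excludes |
| Protocol 9.4 | Not withdrawn: can be traced |
| Protocol 9.5, SAP 3.1.4 | Followed to study end, with agreement |
| Protocol 12.11 | Gives no list of violations, so moving is not named as one |
| SAP 3.5 | In the ITT set |
| SAP 5.3.2 | 1- and 2-year titres belong in the ITT analysis |
| SAP 3.6 | Both titres excluded from analysis |
| SAP 5.2 | Not replaced by imputation |

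The 3.6 rule is the only entry that removes the data.

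**Step 2: reproduce the planned sample sizes.** With equal true rates p, margin 0.10, one-sided 2.5% and 90% power, n per arm = (1.960 + 1.282)² × 2p(1−p) / 0.10².

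- Adults, p = 0.95: 10.51 × 0.095 / 0.01 = 99.8, so 100. The plan states 100, raised by 20% to 120.
- Children, p = 0.90: 10.51 × 0.18 / 0.01 = 189.1, so 190. The plan states 190, raised by 10% to 210.

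**Step 3: drop the movers' late titres.** Power = Φ(0.10 / √(2p(1−p)/n) − 1.96). The half-width of the 95% CI is 1.96 × √(2p(1−p)/n).

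Assumptions not in the documents: 2.5%, 5% or 10% of each randomised arm move and are still sampled; the 10-point margin carries over to late visits; the planned Day 28 rates still hold; 10% of adults are lost by 2 years (120 × 0.90 = 108). For children the plan's own 5% loss is used (210 × 0.95 = 199.5, taken as 200).

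| Cohort and visit | Movers | Dropped per arm (total) | n per arm | Power | Half-width, points |
|---|---|---|---|---|---|
| Adults, 2 years | none | 0 | 108 | 92.1% | 5.81 |
| | 2.5% | 3 (12) | 105 | 91.4% | 5.90 |
| | 5% | 6 (24) | 102 | 90.6% | 5.98 |
| | 10% | 12 (48) | 96 | 88.9% | 6.17 |
| Children, Day 365 | none | 0 | 200 | 91.5% | 5.88 |
| | 2.5% | 5 (10) | 195 | 90.8% | 5.95 |
| | 5% | 11 (22) | 189 | 90.0% | 6.05 |
| | 10% | 21 (42) | 179 | 88.4% | 6.22 |

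Worked line: adults, n = 96: √(0.095/96) = 0.03146; 0.10/0.03146 − 1.96 = 1.219; Φ = 0.889.

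**Step 4: vary the late rate.** If the adult 2-year rate is 90% instead of 95%, power starts at 68.8% (n = 108). It falls to 66.3% with 5% movers (n = 102) and 63.7% with 10% (n = 96). The cost is then up to 5.1 points, from a weaker base.

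**The case against.** The strongest reply is that the rule has almost nobody to act on. People planning to migrate are excluded at entry, no off-site sampling is described, and blood must be processed within 24 hours at one of two laboratories. On that view the example describes someone who has left, with data kept up to departure, which is ordinary handling of loss to follow-up. This stands as an argument about size. It does not rescue the wording: for someone who has left for good the rule is redundant, so its only effect falls on those who come back.

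Second, the plan hints that ITT exclusion was not intended. The ITT definition is specific, the only planned exclusion listing (Listing 1.5) concerns the PP populations, and the deviation listing is reviewed blind before the database is frozen. These hints are real, but 3.6 says analysis without qualification. Blind review guards against arm-driven decisions and does not cancel a written rule. A PP-only reading would also leave the rule idle at the late visits, where the analyses are in the ITT set.

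Third, leaving the area could signal revaccination or different flavivirus exposure, either of which would contaminate a durability titre. Protocol 10.9 does encourage yellow fever vaccination for travel or in an epidemic. This is the best scientific reason for some rule. It supports censoring at the vaccination or infection, which can also happen to people who stay. Some unrecorded exposure would remain.

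Finally, the trial was sized only for Day 28 seroconversion, so the plan states no late-visit power to lose. That is correct: the power figures are illustrations under assumed rates, not estimates of harm.

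**Conclusion.** The concern holds. As written, SAP 3.6 discards valid Day 365 and Day 730 titres that the rest of the plan goes on collecting and assigns to the ITT analysis. Under the assumed 2.5% to 10% of traceable movers, adult 2-year power falls by 0.7 to 3.2 points and the CI half-width grows by about 0.1 to 0.4 points. The children's Day 365 figures are similar. The true moving rate cannot be read from the documents and, given the entry criterion on migration, is probably towards the low end or below it.

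Because participants and follow-up staff are blinded, there is no reason to expect moving to depend on dose, and no direction of bias is claimed. The Day 28 primary analysis, and the choice of dose for children that rests on Day 28 data, are barely affected. This is an avoidable loss of secondary data and an internal contradiction in the SAP, worth correcting because the correction costs almost nothing.

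**What to change.** In SAP 3.6, delete moving away as the example of a partial deviation and add a statement such as: *Moving out of the study area is not in itself a reason to exclude data; samples and safety data collected after a move remain in the ITT and Safety analyses. Titres are censored from the date of a documented non-study yellow fever vaccination or yellow fever infection.* As an optional consistency edit, change and/or to and in the corresponding bullet of SAP 3.1.4, to match protocol 9.4.

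The cost is one or two sentences before database lock, with no new visits, data or sample size. Protocol 8.2.4 already has participants asked about concomitant interventions at scheduled visits, so a later yellow fever vaccination can be identified. The downside is that a few retained titres may reflect vaccination or exposure elsewhere that was never recorded.
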